## Abstract

**Background:**

Health information exchange (HIE) is the electronic sharing of data and information between clinical care and public health entities. Previous research has shown that using HIE to electronically report laboratory results to public health can improve surveillance practice, yet there has been little utilization of HIE for improving provider-based disease reporting. This article describes a study protocol that uses mixed methods to evaluate an intervention to electronically pre-populate provider-based notifiable disease case reporting forms with clinical, laboratory and patient data available through an operational HIE. The evaluation seeks to: (1) identify barriers and facilitators to implementation, adoption and utilization of the intervention; (2) measure impacts on workflow, provider awareness, and end-user satisfaction; and (3) describe the contextual factors that impact the effectiveness of the intervention within heterogeneous clinical settings and the HIE.

**Methods/Design:**

The intervention will be implemented over a staggered schedule in one of the largest and oldest HIE infrastructures in the U.S., the Indiana Network for Patient Care. Evaluation will be conducted utilizing a concurrent design mixed methods framework in which qualitative methods are embedded within the quantitative methods. Quantitative data will include reporting rates, timeliness and burden and report completeness and accuracy, analyzed using interrupted time-series and other pre-post comparisons. Qualitative data regarding pre-post provider perceptions of report completeness, accuracy, and timeliness, reporting burden, data quality, benefits, utility, adoption, utilization and impact on reporting workflow will be collected using semi-structured interviews and open-ended survey items. Data will be triangulated to find convergence or agreement by cross-validating results to produce a contextualized portrayal of the facilitators and barriers to implementation and use of the intervention.

**Discussion:**

By applying mixed research methods and measuring context, facilitators and barriers, and individual, organizational and data quality factors that may impact adoption and utilization of the intervention, we will document whether and how the intervention streamlines provider-based manual reporting workflows, lowers barriers to reporting, increases data completeness, improves reporting timeliness and captures a greater portion of communicable disease burden in the community.

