### Setting

The intervention will be implemented within one of the largest and oldest HIE infrastructures in the U.S., the Indiana Network for Patient Care (INPC). The INPC is anchored by the Regenstrief Medical Record System which collects data from a variety of sources, including hospitals, clinics, pharmacies, and laboratories
[19]. Lab results are routinely delivered to ordering physicians using the Regenstrief DOCS4DOCS® software and analyzed as ELR transactions by the Notifiable Condition Detector (NCD) which identifies mandated reportable diseases and notifies local and state public health departments of these laboratory results
[20].

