### Participants

The study will include outpatient INPC primary care practices operating in urban and rural settings that are part of the INPC, representing multiple health systems and clinics. Clinics that do not use the DOCS4DOCS® software will be excluded.

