### Intervention

Two technical interventions will be deployed over a staggered schedule at participating clinics: 1) “standard” pre-populated forms and 2) “enhanced” pre-populated forms. The “standard” forms intervention will use EHR (patient demographics and clinic information) and ELR (notifiable disease test results) data available in the HIE to pre-populate and deliver an electronic version of the official state notifiable disease reporting form to the provider. Providers will be able to review the pre-populated form, add any additional information, and fax completed forms to their local health department. The “enhanced” forms intervention will pre-populate an alternative reporting form with an expanded set of data available in the HIE. For example, the “enhanced” form will not only include test results data for a case of hepatitis B but also corollary results on the patient’s liver enzymes; this is information the health department typically requests from the provider in a follow-up phone call when investigating the reported case of hepatitis. Providers will still be able to review the pre-populated “enhanced” form, add any additional information, and fax completed forms to their local health department. Since deployment is staggered, at any point in time the non-intervention sites can act as natural controls for the intervention sites without the selection bias that is generally present in non-randomized experiments. Therefore, the study protocol is theoretically equivalent in its ability to generate causal evidence to a traditional randomized controlled experiment.

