### Research questions

Mixed methods studies require that research questions be linked to and drive the data collection and analysis methods, as well as inform the study design, sample size, sampling, instruments developed and administered, and data analysis techniques
[21]. Our primary research questions are:

1. What individual, organizational and data quality factors may act as barriers or facilitators to the successful adoption and utilization of pre-populated reporting forms and enhanced data transaction processing to public health; and

2. What is the relationship of these barriers and facilitators to fostering improvements in provider-based population health reporting workflows, lowering barriers to reporting and case follow-up, increasing data completeness, and enabling greater capture of communicable disease burden in the community?

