### Data collection

Using a concurrent mixed methods design, data collection will be conducted during the three project phases: baseline or pre-implementation; post-implementation of the standard form; and post-implementation of the enhanced form. In each phase, qualitative and quantitative data are collected in tandem as coordinated but independent studies. This design will allow us to triangulate the quantitative results from surveys, time-series, and data quality measures with qualitative interview and open-ended survey results to understand experiences with public health reporting before and after each form implementation. Table 
1 summarizes the categories of data collected.

**Table 1 T1:** Summary of study constructs, data collection, analysis approaches and outcomes measurements by method (qualitative, quantitative)

**Evaluation construct**	**Data collected**	**Tool/method**	**Analysis**
Reporting rates	Provider reports to public health	C	ITS
Completeness	Completed/missing provider report data fields	C	ITS
	Comparison of completeness between S & E forms	C	PPC
	Perceptions of completeness of pre-populated forms	S/I	QUAL/DESC
Accuracy	Inaccurate provider report data fields	C	ITS
	Comparison of accuracy between S & E forms	C	PPC
	Perceptions of accuracy of intervention	S/I	QUAL/DESC
Timeliness	Time between patient diagnosis & treatment	C	ITS
	Time between between lab-confirmed diagnosis & report to public health	C	ITS
	Comparison of timeliness between S & E forms	C	PPC
	Perceptions of timeliness of intervention	S/I	QUAL/DESC
Burden	Volume & duration of phone & Fax communications	C	ITS
	Perceptions regarding reporting burden	S/I	QUAL/DESC
Data Quality	Perceptions regarding quality of data in pre-populated reporting forms	S/I	QUAL/DESC
Form Enhancement	Supplementary data & fields of value to public health	FG	QUAL/PPC
Benefits & Utility	Perceived benefits & utility of intervention	S/I	QUAL/DESC
Adoption & Use	Perceived barriers & facilitators to adopting & using pre-populated report forms	S/I	QUAL/DESC
	Level of acceptance & satisfaction with intervention	S/I	QUAL/DESC
	Perceived ease of operations	S/I	QUAL/DESC
	Acceptability of interface	S/I	QUAL/DESC
Workflow	Public health workflow observations	O	DESC
	Reported impact of intervention on work & information flows	S/I	QUAL/DESC
Context	Clinic demographics	S/I	DESC

KEY.

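### A rise in provider reports cannot by itself show greater capture of community disease burden, because the exchange already notifies public health of the laboratory results that feed the form

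*Protocol article*

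**What the plan says.** - **Aim.** The Discussion paragraph of the Abstract, and the main Discussion in the same terms, say the study will document whether and how the intervention "captures a greater portion of communicable disease burden in the community". Under Research questions, the second primary question includes "enabling greater capture of communicable disease burden in the community".
- **What public health already receives.** Under Setting, the Notifiable Condition Detector analyses laboratory results and "identifies mandated reportable diseases and notifies local and state public health departments of these laboratory results". This runs apart from any form.
- **What feeds the form.** Under Intervention, the standard form "will use EHR (patient demographics and clinic information) and ELR (notifiable disease test results) data available in the HIE to pre-populate and deliver" the state form. The electronic laboratory data are the only source of disease information listed there. The enhanced form "will not only include test results data for a case of hepatitis B but also corollary results on the patient’s liver enzymes", which is more data on the same kind of case.
- **Who takes part.** Under Participants: "Clinics that do not use the DOCS4DOCS® software will be excluded". Setting names this software as the one that delivers laboratory results to ordering physicians.
- **What is measured.** In Table 1 the reporting-rate construct is "Provider reports to public health", taken from a census of report forms and analysed by interrupted time-series. Quantitative data collection defines it as a daily number of reports, by disease and in aggregate. Neither place mentions removing cases already known from a laboratory notification.

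**The concern.** Most cases that can yield a pre-populated form are, on the description given, cases whose laboratory result has also gone to the health department. Background describes this dual structure, in which provider and laboratory report the same disease separately. A successful form should therefore raise provider reports mainly by adding a second notification to cases that public health already knows.

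The article names no other outcome from which capture could be judged. If the report count is used for that purpose, part of the second primary question could be answered yes when the number of distinct cases known to public health has barely moved. A provider-report rate per laboratory-detected case would not cure this, because every case in that denominator has been detected already.

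**Working it through.** The article gives no figure for capture, so there is nothing to reproduce. The check is an identity with illustrative numbers.

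**Notation**
- L: laboratory-detected cases. U: cases with no electronic laboratory result.
- p and q: probability of a provider report for L and U cases.
- e: share of laboratory-detected cases whose notification reaches public health.

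**Formulas**
- Provider reports: R = L·p + U·q.
- Distinct cases known from either source: K = L·[1 − (1 − e)(1 − p)] + U·q, taking provider reporting as independent of whether the laboratory notification arrives.
- Share known: K / (L + U).

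**Inputs.** The starting levels come from Background: about 79% for sexually transmitted infections, and below 50% for diseases such as pertussis, for which 50% is used. They serve as illustration only. Everything else is assumed: L = 1,000; U = 0 or 300; e from 0.90 to 1; p rising to 100%; q either unchanged or up 10 points (spill-over).

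| Case | U | e | p | q | Reports R | Change in R | Share known | Gain (points) |
|---|---|---|---|---|---|---|---|---|
| 1 | 0 | 1 | 50→100% | – | 500→1,000 | +100% | 100→100% | 0 |
| 2 | 0 | 0.90 | 50→100% | – | 500→1,000 | +100% | 95.0→100% | 5.0 |
| 3 | 0 | 1 | 79→100% | – | 790→1,000 | +26.6% | 100→100% | 0 |
| 4 | 0 | 0.95 | 79→100% | – | 790→1,000 | +26.6% | 98.95→100% | 1.05 |
| 5 | 300 | 1 | 79→100% | 79% | 1,027→1,237 | +20.4% | 95.2→95.2% | 0 |
| 6 | 300 | 1 | 79→100% | 79→89% | 1,027→1,267 | +23.4% | 95.2→97.5% | 2.3 |
| 7 | 300 | 1 | 50→100% | 50% | 650→1,150 | +76.9% | 88.5→88.5% | 0 |
| 8 | 300 | 1 | 50→100% | 50→60% | 650→1,180 | +81.5% | 88.5→90.8% | 2.3 |

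Worked lines:
- Case 2, before: 1 − 0.10 × 0.50 = 0.95. After: 1 − 0.10 × 0 = 1. Gain 5.0 points.
- Case 4, before: 1 − 0.05 × 0.21 = 0.9895. Gain 1.05 points.
- Case 6, after: (1,000 + 300 × 0.89) / 1,300 = 1,267 / 1,300 = 97.5%.

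**Reading the table.** Cases 1 and 2 have identical report counts but gains of 0 and 5.0 points. Cases 3 and 4 also share a count and differ in gain. Cases 5 and 6 differ by only 3 percentage points in the rise of the count (20.4% against 23.4%), yet one has no added capture and the other has some. The count does not determine the gain.

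**The case against.** Several points on the other side have force.

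- **The trigger is not stated.** The Intervention section lists what fills the form, not what causes one to be issued. The Abstract and Background speak more broadly of clinical, laboratory and patient data. That a form arises only from a laboratory notification is thus an inference, though no other route is described.
- **Laboratory notification may be incomplete.** Setting does not say that every result is detected and delivered. A reader might infer that the design can never show added capture, or that the gain must be zero. The documents support neither. Missed notifications, or spill-over to cases without an electronic result, could add real cases, as cases 2, 4, 6 and 8 show.
- **Capture may mean capture by provider reporting.** Background frames the goal as improving provider reporting beyond what laboratory reporting has achieved, and notes that laboratory reports lack clinical detail. On that meaning the outcome fits. But the stated aim concerns disease burden in the community, and Background itself credits electronic laboratory reporting with raising the proportion of notifiable disease reports that reach public health.
- **No sentence says a higher count will be read as greater capture.** True. Yet the article promises to document capture and offers no closer outcome. The daily count under Quantitative data collection is not expressly confined to provider reports, unlike Table 1. If laboratory reports were added without de-duplication, one case could still count twice.
- **Linkage may be in the full protocol.** It may, and Table 1's interval from laboratory confirmation to report already needs much of it. That lowers the cost of the fix, but it does not make the stated count a measure of capture.
- **Weight.** Capture is absent from the hypotheses and the evaluation objectives, Background calls it only a potential benefit, and no stated sample size rests on it. This limits the importance of the point.

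**Conclusion.** The point holds in this form: with the measure described, greater capture of community disease cannot be shown by a rise in provider reports alone. The count combines repeat notifications with newly known cases and gives no means of separating them. In the illustrations, the count rises by 20.4% to 100%, while the share of cases known to public health rises by 0 to 5.0 points. These sizes rest on assumed case numbers, reporting levels and delivery rates, and on independence of the two reporting routes. The zero gains further require complete laboratory notification and no spill-over, which the article does not assert.

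The sponsor should act on this, because part of a primary research question depends on it. Analyses of completeness, accuracy, timeliness and communication burden are not affected, and the count remains a valid measure of provider reporting activity.

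**What to change.** 1. Use the link between report and laboratory result that the Table 1 timeliness outcome already needs, and match each provider report to Notifiable Condition Detector notifications by patient and condition.
2. Report two outcomes: (a) distinct cases known to public health from either source after de-duplication, showing provider-reported cases with no laboratory notification as a separate component; (b) the share of laboratory-detected cases that also have a provider report.
3. Rest any claim of greater capture on (a). If (a) stays flat while (b) rises, that is an informative result: better provider reporting without added capture.
4. Otherwise reword the aim in the Abstract, under Research questions and in the Discussion as improved provider reporting of detected cases.

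Outcome (a) removes duplicates but does not supply the true number of cases in the community. It can also move with incidence or testing, so it should be read against clinics that have not yet received the form.

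The cost is one matching and de-duplication step and a less ambitious stated benefit.

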## Background

Health information exchange (HIE) is the capacity to electronically transfer and share health information among health care-related stakeholders and organizations such as clinics, laboratories, payers, hospitals, pharmacies and public health
[1]. HIEs promise to reduce health care costs
[2], improve patient safety
[3], and provide access to more timely surveillance data for public health organizations
[4]; however the success of HIE implementations and their system improvements can depend on the context in which data flow and clinical care workflow are integrated. For example, an investigation of one HIE’s impact on emergency department (ED) charges reported a reduction of approximately $26 per encounter (*p* = 0.03) at one hospital with no effect on charges at a second independent hospital in the same HIE
[5]. Similarly, in a comparison of HIE utilization among municipalities, Maenpaa et al. (2012) reported a difference in system usage between specialized and primary care providers depending on the numbers of ED visits, laboratory tests, radiology exams and appointments
[6]. An investigation of HIE usage in EDs and ambulatory clinics also found that system utilization varied by site, patient population and characteristics, specialization of services, and site policies governing use and administrative access
[7]. Studies such as these suggest that outcomes resulting from HIE interactions, access and interventions can be context-sensitive.

An unexplored area is reporting of communicable and infectious diseases, such as pertussis, tuberculosis, salmonella, Chlamydia and Hepatitis C, among others, to public health in an HIE. Most states utilize a dual reporting structure: mandatory case reporting of a disease by providers and mandatory reporting of test results by laboratories to public health authorities. Conventional provider-initiated paper-based reports, transmitted through fax and mail, have been shown to be incomplete, error-prone and untimely. Report completeness ranges from 9 to 99 percent
[8]. Highly prevalent diseases like sexually transmitted infections are reported approximately 79 percent of the time and many diseases like pertussis and Lyme disease are reported less than 50 percent of the time
[8]. Report timeliness of reporting ranges from one day to three weeks after diagnosis, depending on the disease
[9]. In addition, provider reports often lack demographic details that public health workers need, requiring them to perform follow-up calls to get this additional information
[10].

In comparison to conventional paper-based reporting, electronic laboratory reporting (ELR) has been successful in delivering more timely laboratory test results to public health
[11] and increasing the proportion of notifiable disease reports that are reported to public health
[11,12]. However, implementation of ELR can increase or exceed local investigative capacity by significantly increasing the volume of reported cases to public health agencies
[13,14] and, like provider reports, ELR can lack clinical and treatment details, such as complete patient demographics, vital signs, pregnancy status or prescribed drugs, needed to fully characterize or prioritize a case for public health purposes
[15,16].

Integration of ELR into electronic health record (EHR) systems and HIE networks—i.e., an ELR-EHR-HIE infrastructure—has been shown to connect clinical and public health stakeholders without interrupting existing workflows or adding burden to clinical providers
[17]. Given that many states have (or will have in the near future) an infrastructure supporting ELR and HIE
[18] and EHRs contain clinical and treatment data often missing from ELR, there is potential to use an integrated ELR-EHR-HIE infrastructure to improve provider-based notifiable disease reporting beyond existing improvements to lab-based reporting.

The “Improving Population Health through Enhanced Targeted Regional Decision Support” study aims to leverage an available ELR-EHR-HIE infrastructure to electronically pre-populate provider-submitted notifiable disease report forms with available clinical, lab and patient data. This intervention has the potential to streamline provider-based reporting workflows, lower barriers to reporting, increase data completeness, improve reporting timeliness and capture a greater portion of communicable disease burden in the community.

We hypothesize clinics that implement the intervention will effectively incorporate the pre-populated reporting form into their workflow, providers will report high satisfaction with the intervention, and that, compared to clinics in which the intervention is not implemented, barriers to reporting will be reduced, timeliness of reporting and completeness of report data fields will improve, and need for providers to provide supplemental or corrected data to public health will be reduced. The implementation of the intervention will be evaluated using mixed methods. The study protocol described will evaluate the implementation of the pre-populated form intervention in the context of an operational HIE.

## Methods/Design

The evaluation-specific objectives are to assess the implementation of the reporting form intervention at the clinic level to: (1) identify barriers and facilitators to implementation, adoption and utilization of the pre-populated reporting form; (2) measure impacts of the tool on workflow, provider awareness, and end-user satisfaction; and (3) describe the contextual factors that impact the effectiveness of the intervention within heterogeneous clinical settings and the HIE.

### Setting

The intervention will be implemented within one of the largest and oldest HIE infrastructures in the U.S., the Indiana Network for Patient Care (INPC). The INPC is anchored by the Regenstrief Medical Record System which collects data from a variety of sources, including hospitals, clinics, pharmacies, and laboratories
[19]. Lab results are routinely delivered to ordering physicians using the Regenstrief DOCS4DOCS® software and analyzed as ELR transactions by the Notifiable Condition Detector (NCD) which identifies mandated reportable diseases and notifies local and state public health departments of these laboratory results
[20].

